## Abstract

**Background:**

As minimally invasive surgical techniques have evolved, foraminoscopy has emerged as a predominant surgical procedure. This technique utilizes the intervertebral foramen as the primary surgical pathway and addresses lumbar intervertebral disk issues through endoscopic intervention. However, since the surgery is performed under local anesthesia, achieving satisfactory anesthesia poses significant challenges. This investigation sought to assess the efficacy and comparative differences between two non-pharmacological analgesic approaches: transcutaneous electrical nerve stimulation (TENS) and trans-auricular vagus nerve stimulation (taVNS), in the context of monitored anesthesia care (MAC) during foraminoscopy.

**Methods:**

This investigation adopted a randomized, double-blind, controlled trial design. The participants were randomly divided into the TENS group and the taVNS group. Each group was further divided into three stimulation modes: continuous wave, intermittent wave, and dense–sparse wave. In each group, electrical stimulation was applied 30 min prior to surgery. The main parameters to be evaluated included the patients’ Visual Analogue Scale (VAS) scores, heart rate variability (HRV), bispectral index (BIS), Modified Observer’s Assessment of Alertness/Sedation Scale (MOAA/S) and the supplemental use of oliceridine fumarate during the surgery.

**Discussion:**

This study explores the effect of non-pharmacological electrical stimulation techniques in MAC during foraminoscopy through a randomized controlled trial. If proven effective, these techniques could provide viable non-pharmacological analgesic alternatives for foraminoscopy procedures. Additionally, by comparing different waveform stimulations, the electrical stimulation parameters can be further optimized.

## 1 Introduction

Foraminoscopy represents a minimally invasive spinal surgical procedure. In the treatment of lumbar intervertebral disks, it mainly adopts percutaneous endoscopic lumbar discectomy, which has the advantages of minimal trauma, rapid recovery, clearer surgical field, and enhanced safety (1). Performing foraminoscopy under local anesthesia has the merits of low anesthetic risk, higher precision, and the ability for patients to communicate with doctors during the operation (2). However, since local anesthesia may not completely eliminate discomfort during the surgery, it can increase patients’ nervousness and discomfort. Therefore, there is room for optimization in the anesthesia method. In response to this, different modes of electrical stimulation are considered as adjuvant analgesia in the anesthesia plan.

The technique is termed MAC when an anesthesia practitioner monitors a patient receiving local anesthesia and/or administers sedative-analgesic medications to patients undergoing diagnostic or therapeutic procedures (3). MAC administered in conjunction with local anesthesia provides patients with moderate sedation and analgesia. This effectively alleviates anxiety and intraoperative discomfort, enhances patient cooperation, and offers advantages over general anesthesia, including reduced dosage of sedative and analgesic medications and faster postoperative recovery (4). Currently, MAC serves as the preferred technique for various procedures both inside and outside the operating room, including ophthalmic surgery, otolaryngologic (ENT) surgery, pain procedures, and endoscopy. However, due to the frequent absence of airway protection during MAC, it is crucial to avoid excessive sedation which can lead to central respiratory depression.

The auricular branch of the vagus nerve (ABVN) is the vagus nerve’s only superficial branch, distributed to the auricle, auricular concha, tragus, and other areas. A meta-analysis involving 17 RCTs indicates that 75% of localized auricular acupuncture stimulation primarily targets regions innervated by the ABVN (5). TaVNS exerts modulatory effects on the brain by stimulating the ABVN, thereby influencing the central nervous system (6). In recent years, significant progress has been made in the treatment of chronic pain, epilepsy, and severe depression (7). It has been shown that electrical stimulation of the vagus nerve in the patient’s ear area reduces the frequency of seizures in drug-resistant epilepsy (8), and is thought to have a significant effect on autonomic modulation, which can be effective in controlling pain and sedative effects. In terms of neurophysiology, taVNS activates brainstem centers by stimulating the afferent fibers of the ABVN, thereby enhancing efferent parasympathetic nerve activity. This process increases acetylcholine release onto the sinoatrial node of the heart, leading to reduced heart rate and increased vagally-mediated HRV (9). The precise mechanisms and effects of taVNS are not yet fully understood. Preliminary research suggests that taVNS may stimulate the cholinergic anti-inflammatory pathway, resulting in reduced production of pro-inflammatory cytokines (e.g., IL-1β, IL-6), thereby exerting anti-inflammatory effects (10). It may also modulate noradrenergic activity in the locus coeruleus (LC), consequently influencing the body’s autonomic nervous system (11). Furthermore, no consensus has been reached regarding the optimal stimulation duration, the most effective sites for stimulation, or the ideal stimulation parameters (12).

Peripheral nerve stimulation (PNS) modulates pain signaling by directly stimulating peripheral nerves in the limbs, primarily affecting the peripheral nervous system. TENS based on the Gate Control Theory, utilizes high-frequency, low-intensity stimulation to activate large-diameter Aβ afferent fibers. This induces segmental inhibition of nociceptive signal transmission at the level of the spinal cord dorsal horn (13). Contemporary applications frequently combine TENS with traditional Chinese acupuncture for acupoint electrical stimulation in pain management, proving effective for various chronic pain conditions. For example, Mu et al. (14) demonstrated that electrical stimulation at the Zusanli acupoint can relieve abdominal pain after gastrointestinal surgery; Zhang et al. (15) analyzed relevant articles and concluded that percutaneous acupoint electrical stimulation can improve the postoperative analgesic effect of patients under general anesthesia and reduce the incidence of postoperative nausea and vomiting. Simultaneously, (16) studies in lumbar orthopedic surgery have indicated that electrical stimulation applied at the Neiguan (PC6) and Hegu (LI4) acupoints, when used as an adjunct to general anesthesia, effectively maintains heart rate stability and reduces the surgical stress response in patients undergoing open posterior lumbar spine surgery. However, more high–quality research is urgently needed to further explore its application in monitored anesthesia and provide patients with more personalized and comfortable analgesic plans.

Oliceridine fumarate is a novel G protein-biased ligand μ-opioid receptor agonist. Approved by the FDA in 2020, it represents the first intravenously administered opioid medication approved by the agency in decades. Relevant studies have demonstrated its potent analgesic efficacy, with onset and duration of action comparable to morphine (17–19).

Compared to traditional opioids such as morphine and fentanyl—which, while effective for pain relief—are frequently limited by opioid-related adverse events (AEs) including respiratory depression, nausea, vomiting, ileus, and excessive sedation (20), clinical studies indicate improved safety profiles for oliceridine versus morphine (21, 22). Consequently, it holds promise as a new alternative for analgesia during MAC.

This study investigates the combined application of electrical stimulation and oliceridine fumarate injection into MAC, studies the differences in the effects of TENS and taVNS on patients’ heart rate variability, Visual Analogue Scale scores, and bispectral index, explores the differences in the efficacy of different waveforms in monitored anesthesia, expands the application scope of transcutaneous electrical stimulation, further optimizes the electrical stimulation parameters, and simultaneously explores the reduction of the dosage of oliceridine fumarate injection under different stimulations to improve the effect of monitored anesthesia technology, thereby providing patients with more comfortable and personalized plans.

## 2 Materials and methods

### 2.1 Study design

#### 2.1.1 Trial design

This experiment is designed as a randomized controlled clinical trial (RCT). The research subjects are surgical patients undergoing foraminoscopy under monitored anesthesia in Hebei General Hospital. The effects of TENS and taVNS are compared through random grouping. This research protocol is written in accordance with the recommendations of the Standard Protocol Items: Recommendations for Interventional Trials (SPIRIT).

#### 2.1.2 Study setting

This study will be conducted in the Department of Anesthesiology, Hebei General Hospital, China.

#### 2.1.3 Participants

All participants will be strictly screened according to the inclusion and exclusion criteria. Researchers will introduce the experimental procedures, consent forms, and the established plans in detail to the subjects. Eligible volunteers will be invited to participate in the study. After signing the informed consent form, they will undergo a baseline assessment.

#### 2.1.4 Eligibility criteria

##### 2.1.4.1 Inclusion criteria

•Aged 18–65 years old, conscious and with civil capacity, and having no contraindications to surgery and anesthesia.•Signed the informed consent form.

##### 2.1.4.2 Exclusion criteria

•Patients with severe respiratory depression, gastrointestinal obstruction, severe arrhythmia, severe liver insufficiency.•Patients who experience severe adverse reactions during the operation and have the operation terminated or the anesthesia method changed.•Patients with neurological diseases such as epilepsy or a history of epilepsy.•Patients known to be allergic to oliceridine.•Patients with skin infections or damage at the stimulation site.

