### 2.2 Randomization and blinding

Patients are divided into two groups (TENS group and taVNS group) through a random number table generated by a computer. Each group is designed with a control group and three stimulation subgroups. A double–blind design is adopted, and neither the interveners (personnel implementing electrical stimulation interventions) nor the patients are aware of the grouping situation. They do not have access to the group allocation sequence, are not involved in randomization procedures, and do not participate in outcome assessments. To ensure effective blinding, all electrode pads will be covered with identical opaque adhesive membranes, with only the conductive contact point exposed. Additionally, electrode pads will be applied to both the auricular and acupoint regions in all participants, regardless of group allocation. As a result, the interveners will not know which site is actively receiving stimulation.

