#### 2.4.2 Intervention description

Based on a systematic review and related studies (23), each group receives 30-min corresponding stimulation or placebo intervention before surgery. The current intensity is adjusted to the maximum tolerance of the patient, the pulse width is fixed at 200 μs, and the frequency is fixed at 30 Hz. When patients with severe pain cannot tolerate it, oliceridine fumarate injection is supplemented to the subjects. The supplementary standard is: a single dose of 0.35 mg–0.50 mg, intravenous injection, and the dosing interval is not less than 6 min.

•TENS Group: Electrodes are placed at the bilateral Neiguan and Hegu acupoints of the subjects. Hegu (LI4): Located on the dorsum of the hand, between the 1st and 2nd metacarpal bones, at the midpoint of the radial side of the second metacarpal bone. Neiguan (PC6): Located on the palmar aspect of the forearm, 2 cun proximal to the transverse wrist crease, between the tendons of the palmaris longus and the flexor carpi radialis muscles.•TaVNS Group: Electrodes are placed at the bilateral tragus of the subjects.

Each stimulation group was further subdivided into following stimulation modes:

•Continuous Wave Group: Given 30-min continuous electrical stimulation.•Intermittent Wave Group: Subjects receive 30-min intermittent electrical stimulation (stimulate once every 15 s, with an interval of 5 s).•Dense-Sparse Wave Group: Subjects receive 30-min variable–frequency electrical stimulation (sparse wave 6 Hz, dense wave 30 Hz).•Control Group: Electrode patches are placed but not energized, making the patients psychologically believe that they have received stimulation.

The experimental process is shown in Figure 1.

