## 4 Discussion

HRV refers to the variation in time intervals between consecutive heartbeats and is mainly controlled by the cardiac autonomic nerves. It has been widely recognized as an effective indicator for evaluating autonomic nerve function.

The application of TENS and taVNS represents an emerging analgesic, sedative, and neuromodulatory strategy during foraminoscopy. These two non-pharmacological, minimally invasive modulation techniques are considered potentially beneficial for optimizing perioperative management, though their effects require cautious evaluation. Both modalities deliver electrical currents via stimulators, constituting a primary source of electromagnetic interference. Consequently, they are contraindicated in patients with implantable cardioverter defibrillators (ICDs), with interference levels demonstrating significant correlation to stimulation parameters that necessitate strict control (28). Additionally, substantial challenges exist in parameter selection due to individual variability in:neural sensitivity to stimulation, stimulation tolerance thresholds, psychological factors. Electrode placement for TENS should avoid surgical fields to prevent contamination. Notably, high-quality clinical studies investigating TENS and taVNS applications during MAC for transforaminal endoscopy remain limited. This study aims to provide novel clinical data in this domain.

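### The article calls both trial interventions contraindicated with an implanted cardioverter defibrillator (ICD), but its exclusion list does not name ICDs

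*Protocol article*

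**What the plan says.** Section 4 (Discussion) names the stimulators used for both modalities as a source of electromagnetic interference and concludes that "they are contraindicated in patients with implantable cardioverter defibrillators (ICDs". The same sentence adds "interference levels demonstrating significant correlation to stimulation parameters that necessitate strict control".

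Section 2.1.3 makes the eligibility lists the working screen: "All participants will be strictly screened according to the inclusion and exclusion criteria".

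The items in those lists that bear on this point are:

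- Section 2.1.4.1 (inclusion) requires "having no contraindications to surgery and anesthesia".
- Section 2.1.4.2 (exclusion) has one item with cardiac content: "Patients with severe respiratory depression, gastrointestinal obstruction, severe arrhythmia, severe liver insufficiency".
- Section 2.1.4.2 also has one item specific to electrical stimulation: "Patients with skin infections or damage at the stimulation site".

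The other exclusions concern severe intraoperative reactions, neurological disease or epilepsy, and oliceridine allergy. The withdrawal criteria in section 2.1.4.3 concern departures from the anaesthesia protocol, serious adverse events, drugs that alter heart rate, and incomplete monitoring. None of these lists names an ICD, a pacemaker or any other implanted device. ICDs are mentioned only in section 4.

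On delivery, section 2.4.2 says "The current intensity is adjusted to the maximum tolerance of the patient", with pulse width fixed at 200 μs and frequency at 30 Hz. On allocation, section 2.2 says "Each group is designed with a control group and three stimulation subgroups".

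**The concern.** The article states a contraindication to its own interventions and then prints a screen that does not apply it. Staff who follow the printed criteria would have no listed reason to turn away an ICD carrier whose rhythm is controlled at screening.

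What is at stake is the safety of that participant. If allocated to an active subgroup, the patient would receive 30 minutes of current from a device that the article itself says should not be used in such patients. The article also says that interference depends on the stimulation settings, yet current intensity is set by what the patient tolerates and section 2.4.2 states no upper limit. Under section 2.2 those applying the stimulation do not know the allocation or which site is live, so screening before randomisation is the natural place to prevent the exposure.

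**Working it through.** The main check is textual. The arithmetic only sizes the consequence if an ICD carrier is enrolled.

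**Does any printed criterion exclude an ICD carrier?**

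| Criterion | Section | Excludes an ICD carrier? |
|---|---|---|
| Severe arrhythmia | 2.1.4.2 | Only if the patient has severe arrhythmia at screening; a carrier with a controlled rhythm need not |
| Severe respiratory, gastrointestinal or liver conditions | 2.1.4.2 | No |
| Severe reaction during the operation | 2.1.4.2 | No; it applies only after exposure |
| Neurological disease or epilepsy | 2.1.4.2 | No |
| Oliceridine allergy | 2.1.4.2 | No |
| Skin problem where electrodes are placed | 2.1.4.2 | No |
| No contraindication to surgery or anaesthesia | 2.1.4.1 | Only if stimulation is read as part of anaesthesia; the text does not say so |
| Withdrawal criteria | 2.1.4.3 | No; they apply after enrolment and name no device |

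No item excludes an ICD carrier as such. Section 4 ties the hazard to the device and the current, not to the heart rhythm, so the arrhythmia item does not stand in for it.

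**If an ICD carrier were enrolled, how likely is stimulation?**

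Inputs: two sites (TENS, taVNS) and, at each site, three energised modes and one control whose electrodes are not energised (sections 2.2 and 2.4.2); 32 per subgroup and 272 in total (section 2.3).

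- Energised subgroups: 2 × 3 = 6. All subgroups: 2 × 4 = 8. With equal subgroups: 6/8 = 75%.
- The stated subgroup size accounts for 8 × 32 = 256 participants, which leaves 272 − 256 = 16 unassigned.
- All 16 in control subgroups: 6 × 32 = 192, and 192/272 = 70.6%.
- All 16 in active subgroups: 192 + 16 = 208, and 208/272 = 76.5%.
- Equal split: 272/8 = 34 per subgroup, 6 × 34 = 204, and 204/272 = 75.0%.

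The chance of stimulation is therefore about 71% to 76%, however the 16 are placed. The article gives no prevalence of ICDs among foraminoscopy candidates, so an expected number of affected participants cannot be calculated.

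**The case against.** The best counter-argument is that the inclusion criterion on contraindications already covers the case. The Introduction presents electrical stimulation as adjuvant analgesia within the anaesthesia plan, and section 3.5 describes taVNS as a method that assists anaesthesia. On that reading, a contraindication to stimulation is a contraindication to the anaesthesia. The reading is possible, but it is an inference. The exclusion list itemises oliceridine allergy and skin damage at the electrode site separately, so the authors did not leave contraindications to the trial drug or the stimulation to the general clause. A safety exclusion should not depend on each screener drawing the same inference.

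A second objection is that a journal article condenses a fuller protocol, and that the screening form is not shown. It is true that the full protocol or the form may already contain the item. But the article prints its own itemised list and, elsewhere, a contraindication which that list does not apply. That is a mismatch between two printed statements, not a detail left to another document.

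Third, stimulation is not uncontrolled. Pulse width is fixed, and frequency is either fixed or, in the dense-sparse mode, set at 6 and 30 Hz. Only intensity is titrated, and section 4 does not say which settings drive interference. This is fair and softens the contrast with the call for strict control. It does not affect the main point, because section 4 states the contraindication without reference to settings.

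Finally, the event is rare, and nothing in the estimand, sample size, randomisation or analysis depends on it. That stands. The allocation percentages are likewise conditional on an enrolment that may never happen.

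**Conclusion.** The concern holds. The article declares both interventions contraindicated in ICD carriers, and none of its eligibility or withdrawal lists names the device. As printed, the plan would allow an ICD carrier with a controlled rhythm to be randomised, with about a three-in-four chance (71% to 76%) of receiving current titrated to tolerance.

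This rests on two readings: that severe arrhythmia refers to the patient's rhythm and not to an implanted device, and that the clause on surgery and anaesthesia does not by itself extend to electrical stimulation. The frequency of such enrolments is unknown and probably very small. The point should nevertheless be corrected before enrolment, because the hazard is one the article itself recognises and the harm would fall on a participant. The statistical design is not affected.

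**What to change.** Add patients with an implantable cardioverter defibrillator to the exclusion criteria in section 2.1.4.2, and put a matching question on the screening form, answered before enrolment. If the full protocol already has this exclusion, bring the printed list into line with it.

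The article names only ICDs, so that is the minimum change. Whether to extend the exclusion to pacemakers and other implanted electronic devices is a clinical decision for the investigators.

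The cost is one line of text, one screening question and the loss of a probably very small number of candidates. Nothing in the sample size calculation or the analysis needs to change.

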##### 2.1.4.3 Withdrawal criteria

•Deviation from the assigned anesthesia protocol.•Occurrence of any serious adverse event.•Intraoperative administration of heart rate-altering medications (e.g., atropine).•Failure to complete all required monitoring procedures.

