###### 2.4.2.1.1 Criteria for discontinuing or modifying allocated interventions

If a subject withdraws from the experiment midway or is not satisfied with the analgesic effect, the recent data will be calculated for analysis according to the intention–to–treat principle. Conventional drugs will be used for analgesia and sedation management, and the reason for withdrawing from the study will be recorded.

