### 3.3 Methods in analysis to handle protocol non–adherence and any statistical methods to handle missing data

Intention-to-treat analysis will be used, and missing data will be appropriately processed in accordance with established guidelines.

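### An exclusion criterion based on an intraoperative event acts after randomisation and contradicts intention-to-treat, and the withdrawal and recent-data rules leave the analysis set unclear

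*Protocol article*

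**What the plan says.** Four places in the protocol article bear on who is analysed and with which values.

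- **Section 2.1.4.2 (exclusion criteria)** lists "Patients who experience severe adverse reactions during the operation and have the operation terminated or the anesthesia method changed" beside ordinary screening conditions such as epilepsy or a known oliceridine allergy.
- **Section 2.1.4.3 (withdrawal criteria)** has four triggers: "Deviation from the assigned anesthesia protocol"; "Occurrence of any serious adverse event"; "Intraoperative administration of heart rate-altering medications (e.g., atropine" being its example of such a drug; and "Failure to complete all required monitoring procedures".
- **Section 2.4.2.1.1** covers subjects who leave midway or are dissatisfied with their analgesia. For them, "the recent data will be calculated for analysis according to the intention–to–treat principle", and the reason for leaving is recorded.
- **Section 3.3** states: "Intention-to-treat analysis will be used, and missing data will be appropriately processed in accordance with established guidelines".

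The order of events is fixed elsewhere. Section 2.1.3 applies the eligibility criteria at screening. Table 1 puts allocation at T0 and the intervention at T2. Section 2.4.2 gives the 30 minutes of stimulation or placebo before surgery.

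**The concern.** An event during the operation cannot be known at screening. If it is used to exclude, a randomised and fully treated patient leaves the comparison because of something that happened after treatment. Intention-to-treat rules that out.

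The withdrawal triggers raise a related worry. The Introduction says taVNS slows the heart, section 2.5.2 counts bradycardia and hypotension as adverse events, and section 3.5 expects no significant effect of TENS on HRV. A rule triggered by heart-rate drugs therefore sits on a pathway where the article itself expects the arms to differ. If patients leave, or have their outcome replaced by an earlier value, at different rates in the two arms, the VAS, BIS and HRV comparisons lose the protection of randomisation.

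**Working it through.** **1. Order of events (no arithmetic needed).** Screening, then allocation (T0), then stimulation (T2), then the start of the operation (Time 3 in section 2.4.2.1). The intraoperative criterion can first be met after Time 3, so it can exclude only patients who have been randomised and have received their stimulation. Section 3.3 requires those patients to be analysed as randomised. Both statements cannot be carried out.

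**2. Withdrawal and recent data.** Section 2.1.4.3 does not say that withdrawn patients leave the analysis, and section 2.4.2.1.1 keeps their data. It does not say which data. Under one reading, the last available value stands in for later ones. For a patient who leaves early in the operation, that may be the Time 2 value (before surgery) or the Time 3 value (as it starts). Under another reading, values collected so far are simply analysed as they are. Section 3.3 does not decide between them.

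**3. The plan's own figure, as a yardstick.** Section 2.3 gives VAS SDs of 2.5 (taVNS) and 3.0 (TENS) and 121 per group, but no difference and no power. Assuming a difference of 1.0, 80% power and two-sided 0.05:

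n = (2.5² + 3.0²) × (1.960 + 0.842)² / 1.0² ≈ 15.25 × 7.85 ≈ 119.7, so 120.

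The unequal-variance t-test gives 121 (power 0.801). The 1.0-point yardstick is thus inferred, not stated.

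**4. Illustration A: patients removed.** All rates are assumed. If a fraction p is removed and their VAS exceeds the arm mean by d, the arm mean moves by −p·d/(1−p). With d = 2:

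- 10% taVNS, 3% TENS: −0.2/0.90 = −0.222 and −0.06/0.97 = −0.062; net −0.16.
- 15% taVNS, 5% TENS: −0.3/0.85 = −0.353 and −0.1/0.95 = −0.105; net −0.25.

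If the removed patients lie 2 points *below* the arm mean, the signs reverse: +0.16 and +0.25.

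**5. Illustration B: outcomes replaced.** If a fraction p keeps an earlier value that is d below the true later value, the arm mean moves by −p·d. With d = 2:

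- 10% against 3%: −0.20 + 0.06 = −0.14.
- 15% against 5%: −0.30 + 0.10 = −0.20.

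**6. Effect on type I error.** Simulation with 136 per arm, the stated SDs, no true difference, Welch t-test and 5,000 runs. Patients with the highest VAS are removed, either exactly or through a latent score correlated 0.5 with VAS. Differences are taVNS minus TENS.

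| Removed, taVNS / TENS | Tie to VAS | Spurious difference | Type I error |
|---|---|---|---|
| 5% / 5% | exact | +0.05 | 7.3% |
| 5% / 5% | 0.5 | +0.03 | 5.7% |
| 5% / 2% | exact | −0.11 | 7.5% |
| 5% / 2% | 0.5 | −0.05 | 5.2% |
| 10% / 2% | exact | −0.33 | 20.7% |
| 10% / 2% | 0.5 | −0.17 | 8.1% |

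With nobody removed, the simulated error was 5.2% and 4.7%. In these scenarios the distortion becomes large only when removal is frequent, unequal and closely tied to the outcome.

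**7. Sample size.** Section 2.3 inflates 121 to 136, which allows a loss of 15/136 = 11.0% per group. Keeping every randomised patient in the analysis does not increase the planned number.

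**The case against.** Several stronger conclusions are tempting, and the article does not support them.

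- **That withdrawn patients leave the analysis.** Section 2.1.4.3 does not say so, and section 2.4.2.1.1 keeps their data under intention-to-treat. No withdrawal trigger names analgesic failure, and supplementary oliceridine is part of the protocol. The outright contradiction is confined to the intraoperative exclusion criterion.
- **That the worst outcomes are removed selectively by arm, in favour of taVNS.** No arm-specific rates are given. Stimulation ends before surgery, both groups contain an unenergised control subgroup, and such events can also arise from the surgery or the opioid. On the article's own hypothesis, strong vagal responders may have the better VAS and HRV values, so losing them could weaken the apparent taVNS effect.
- **That serious adverse events vanish from the safety comparison.** Section 2.5.2 lists adverse events with no exception for withdrawn patients.
- **That recent data means last observation carried forward.** That is one reading of ambiguous wording.

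It can also be said that the intraoperative bullet is a misplaced withdrawal rule, and that an unseen analysis plan may define the analysis set and the missing-data method. If the bullet is only misplaced, correcting its position resolves the contradiction. As written, however, it is an exclusion, and an analysis plan could not follow both it and section 3.3. The missing-data method may fairly be left to that plan; the conflict may not.

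**Conclusion.** The concern holds in limited form. The intraoperative exclusion criterion is a post-randomisation exclusion and contradicts the intention-to-treat statement. This follows from the text alone and rests on no assumption.

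Beyond that, sections 2.1.4.3, 2.4.2.1.1 and 3.3 do not make the analysis set clear. They allow outcomes to be replaced by earlier values, and one trigger lies on the heart-rate pathway attributed to taVNS. Unequal loss between arms is a credible risk and not an established fact.

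The size and direction of any bias are unknown. The illustrated shifts of 0.14 to 0.25 VAS points depend on assumed loss rates and an assumed 2-point gap. Setting them against a 1.0-point difference adds a further assumption. The conflict should be settled before analysis because it decides who enters the primary comparison.

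**What to change.** 1. Delete the intraoperative bullet from section 2.1.4.2.
2. Reconcile sections 2.1.4.2, 2.1.4.3, 2.4.2.1.1 and 3.3 by separating three things: screening exclusions, discontinuation of the intervention, and the analysis set.
3. State that all randomised patients are analysed in their assigned arm, and that scheduled measurements continue after discontinuation where they can be obtained.
4. Record serious adverse events, use of heart-rate drugs and change of anaesthetic method, and report them by arm for all randomised patients.
5. For HRV only, treat epochs after a heart-rate drug as missing. Keep the patient's earlier epochs and all VAS, BIS and safety data. This meets the legitimate purpose of that withdrawal rule.
6. Replace the recent-data rule by use of the observed later values. Where values are truly missing, use a likelihood-based mixed model or multiple imputation; the details can sit in the analysis plan.

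Cost: a protocol amendment to these sections, with no change to the 136 per group. The measurements are already scheduled, but some patients who would have stopped being measured must now be followed to the end of the operation. Intraoperative scores may be unobtainable if the operation is stopped or the anaesthetic is switched. None of this alters the clinical stopping or rescue rules.
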